### Procedures for recording AEs

Assessment for AEs are to be conducted at each study visit. All AEs occurring during the trial that are observed by the PI/delegate or reported by the participant will be recorded in the eCRF, whether or not attributed to the study drug. In recording the AE on the eCRF, whether the event was an SAE or not will be entered. All AEs determined to be an SAE must be reported following the guidelines and time frames below.

All AEs and SAEs will be followed-up to resolution with a start date and an end date recorded.

It will be left to the PI’s clinical judgement to decide whether or not an AE is of sufficient severity to require the participant’s removal from the trial. A participant may also voluntarily withdraw from treatment due to what she perceives an intolerable AE. If either of these occurs, the participant must be given appropriate care until symptoms cease or the condition becomes stable.

Unexpected serious adverse maternal and neonatal events (SAEs) will be reported to the sponsor within 24 h. The sponsor will forward these reports and their review of the SAE to the DSMC and the HREC that provided REC approval within 72 h of receipt.

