### Withdrawal of participants

It will be made clear to participants that they remain free to withdraw from the clinical trial at any time without the need to provide any reason or explanation; and that this decision will not impact on any aspect of their ongoing clinical care. The investigator will be able to discontinue participants from either of the study drugs in the event that they judge that alternative treatment is required, without the woman being necessarily withdrawn from the study. Participants will not be withdrawn for self-reported low or non-adherence to their study treatment.

Permission will be sought to complete and use data up to the point of withdrawal including both:
trial specific datadata collected as per routine clinical practice

Permission will also be sought to ascertain and record subsequent perinatal outcome data.

The reason for withdrawal will be recorded in the eCRF, and, if it was due to an Adverse Event, the investigator will follow up to resolution/stability.

Similarly, it will also be made clear to participants that they remain free to withdraw from any future sub-studies to which they have agreed at any time without the need to provide any reason or explanation; and that such a decision will not impact on any aspect of their ongoing clinical care.

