### Data analysis

A detailed Statistical Analysis Plan will be developed by the trial statistician (who is independent of the Sponsor) and agreed by the Trial Management Committee (TMC) before the analysis is undertaken. The analysis and presentation of results will follow the most up-to-date recommendations of the CONSORT group. Analyses will be completed in STATA® version 13.0 or later.

All analyses will follow the intention to treat principle, i.e. data from all randomised woman and babies will be analysed according to the treatment they were allocated to irrespective of the treatment they received or whether they received any treatment at all.

Blinding will not be possible for participants and care providers, because of the open nature of the interventions, nor will the DSMC be blinded to allocation in their assessment of outcomes and safety, but the outcome data will be blinded to the data analysts by concealing the group allocation prior to the analysis.

Demographic and clinical data will be summarised with counts and percentages for categorical variables, means (standard deviations) for normally distributed continuous variables and medians (with interquartile or simple ranges) for other continuous variables.

For the primary outcome, the effectiveness of the interventions will be assessed by calculating the differences in mean pruritus score with 95% confidence intervals (CI), determined with a linear regression model, using Generalised Estimating Equations (GEEs).

All comparative analyses will be performed adjusting for stratification variables and baseline measures of the outcome, where relevant. Binary outcomes will be analysed using log binomial regression models. Results will be presented as adjusted risk ratios plus 95% CIs. If the model is unstable, log Poisson regression models with robust variance estimation will be used [34]. Continuous outcomes will be analysed using linear regression models, and results will be presented as adjusted differences in means (with 95% CIs). Analysis of outcomes that are measured repeatedly over time (severity of pruritus and biochemical markers) will use repeated measures analysis techniques, including GEEs and/or random effects.

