### Dealing with missing data

Missing data as a result of women or babies being lost to follow-up are expected to be minimal. A sensitivity analysis will be conducted on the primary outcome and multiple imputation by the fully conditional specification (chained equations) method will be used to impute missing outcome data.

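### Removing a woman from the trial for an adverse event, as worded, is likely to lose later itch scores that the intention-to-treat analysis relies on

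*Protocol article*

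**What the plan says.** The protocol article deals with adverse events that affect participation in two places.

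- **Procedures for recording AEs.** The principal investigator's clinical judgement is used "to decide whether or not an AE is of sufficient severity to require the participant’s removal from the trial". The next sentence describes the woman's own choice in narrower terms: "A participant may also voluntarily withdraw from treatment due to what she perceives an intolerable AE".
- **Withdrawal of participants.** The investigator may stop either study drug "without the woman being necessarily withdrawn from the study". Low adherence is not a reason for withdrawal.

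For a woman who does withdraw, the second section covers two kinds of data. On data already collected: "Permission will be sought to complete and use data up to the point of withdrawal including both" trial-specific and routine clinical data. On what follows: "Permission will also be sought to ascertain and record subsequent perinatal outcome data". Itch is not mentioned.

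The primary outcome is a maternal itch score. Under Secondary outcomes, its schedule is one week after entry, then monthly to 28 weeks of gestation, then weekly to delivery. Data analysis specifies a linear GEE model and intention to treat: "data from all randomised woman and babies will be analysed according to the treatment they were allocated to irrespective of the treatment they received". The same section says "Blinding will not be possible for participants and care providers, because of the open nature of the interventions". Dealing with missing data expects little loss to follow-up and plans a sensitivity analysis on the primary outcome, in which "multiple imputation by the fully conditional specification (chained equations) method will be used to impute missing outcome data".

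**The concern.** Stopping a drug and leaving a trial are different events. An intention-to-treat comparison needs outcomes measured after the first, and can lose them only through the second. The adverse-event section lets the investigator move directly to the second, while the withdrawal section keeps the two apart.

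Three features make the lost scores unlikely to be a random subset. The decision is a judgement about severity. It is made with the allocation known, since Baseline assessments has the randomisation notice go to the site investigator or delegate. And the drugs' listed side effects differ, so the reasons for removal may differ by arm.

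A difference in removal rate alone would not bias the comparison. Bias arises if, within an arm, the later itch of removed women would have differed from that of retained women. That is plausible where removal follows intolerance of a drug that was reducing itch. In general, an unweighted GEE is valid only if such scores are missing completely at random.

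**Working it through.** **Step 1. Does itch scoring end at removal?** No sentence says so; it is an inference from three observations.

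1. Withdrawal of participants names data up to withdrawal and later perinatal outcomes only.
2. The notes to Table 1 follow the same pattern for a separate route, in which a woman on rifampicin starts an interacting medicine: data until withdrawal, then pregnancy outcome.
3. Itch is a maternal outcome, and the perinatal outcomes are listed separately from the maternal ones.

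The documents do continue care and adverse-event follow-up after removal. Nothing continues itch scores.

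**Step 2. What is lost?** Scores before removal are kept, with permission, and a repeated-measures GEE uses them. Only a woman removed before the one-week score has no post-baseline value. The others lose later scores.

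**Step 3. How large could the effect be?** The plan gives no figure for adverse-event removal, so there is none to reproduce. The inputs come from Rationale for sample size: 54 women per arm, 5% drop-out per arm (0.05 × 54 = 2.7 women), and these mean changes:

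- UDCA −16 mm, rifampicin −23 mm: effect 7 mm
- UDCA −16 mm, rifampicin −30 mm: effect 14 mm
- UDCA −5.7 mm, rifampicin −23 mm: effect 17.3 mm

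If a share f of an arm is removed early, the shift in that arm's mean is

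shift = f × (mean reduction in retained women − mean reduction removed women would have shown).

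The plan's means are taken as those of retained women.

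| Assumption, with f = 0.05 | 7 mm effect | 14 mm effect |
|---|---|---|
| Removal late in follow-up | near zero | near zero |
| Rifampicin only, then the plan's UDCA change | 0.05 × (23 − 16) = 0.35 mm (5%) | 0.05 × (30 − 16) = 0.70 mm (5%) |
| Both arms, full return to baseline | 0.05 × 23 − 0.05 × 16 = 0.35 mm (5%) | 0.05 × 30 − 0.05 × 16 = 0.70 mm (5%) |
| Rifampicin only, all early, full return to baseline | 0.05 × 23 = 1.15 mm (1.15/7 = 16.4%) | 0.05 × 30 = 1.50 mm (1.50/14 = 10.7%) |

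For the 17.3 mm effect, the last row gives 1.15/17.3 = 6.6%.

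These shifts favour rifampicin. The direction is not fixed: removal from UDCA only, with return to baseline, gives 0.05 × 16 = 0.80 mm the other way.

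**Step 4. Against the trial's precision.** For a simple comparison of means, SE = SD × √(2/54).

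- SD 10 mm: SE 1.92 mm, so 1.15 mm is 0.60 SE.
- SD 28 mm: SE 5.39 mm, so 1.50 mm is 0.28 SE.

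The plan itself concedes that 10 mm might appear too small.

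**The case against.** The strongest case against is that this is loose wording and not a rule. Withdrawal of participants is the governing section and already separates drug from study. The adverse-event section speaks of treatment in its next sentence and then treats both cases alike. The article is also condensed, so post-withdrawal procedures may be fuller elsewhere. This lowers the importance of the point. It does not remove it, because a site that follows the adverse-event section as printed may end participation, and no text shown then keeps the itch scores.

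Stronger readings are tempting, but the documents do not support them.

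- **The primary analysis loses these women.** It does not, apart from any removed before the one-week score.
- **Intention to treat is contradicted.** The article defines it as analysis by allocated arm, and removal changes neither the allocation nor the analysis set. The shortfall is in the data available.
- **The sensitivity analysis cannot detect the problem.** Only the imputation method is named. Its predictors are not shown, and it could condition on a woman's earlier scores and on stopping treatment.
- **Worsening itch itself triggers removal.** Under Expected events, worsening pruritus and hospitalisation for worsening disease are not reported as adverse events.
- **The bias is 16% of the effect.** That needs every drop-out to be an early adverse-event removal, none in the UDCA arm, and complete return of itch. Current practice says women with severe disease are usually offered UDCA, so full return to baseline is far from assured.

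**Conclusion.** The point holds as a cheap improvement. The two sections are inconsistent on whether an adverse event ends treatment or participation. With only perinatal data named after withdrawal, itch scores after removal are likely to be lost for treatment-related reasons that may differ by arm.

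The effect on the primary result is uncertain and probably small. At 5% drop-out it runs from near zero, through about 0.35 to 0.7 mm (5% of the effect), to 1.15 to 1.5 mm (11 to 16%) as an upper bound for that drop-out under the most adverse assumptions tabulated for rifampicin. All of these rest on assumed timing, arm and later itch, none of which the documents give. The shift scales in proportion if removals exceed 5%.

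**What to change.** Reconcile Procedures for recording AEs with Withdrawal of participants on three points.

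1. An adverse event may lead to study drug being stopped, a decision that stays wholly with the investigator, but does not by itself end participation.
2. Itch scoring then continues on the planned schedule to delivery unless the woman withdraws consent to data collection.
3. Those later scores are analysed as allocated in the primary GEE.

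How to impute scores for women who do withdraw consent can be left to the statistical analysis plan.

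The cost is a wording amendment and one 100 mm scale per visit for a few women. The estimate may become slightly less favourable to rifampicin. The Discussion says recruitment is underway, so the change is worth making promptly: scores not collected cannot be recovered at analysis.

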### Treatment stopping rules

After inclusion of 50 women in the cohort, the DSMC will assess safety issues to ensure there is no convincing evidence of harm in either arm of the study. The DSMC will, if appropriate, make recommendations regarding continuance of the study or modification of the study protocol.

The trial management committee (TMC) has ultimate responsibility for deciding whether a trial should be stopped on safety grounds and will meet regularly to ensure recruitment milestones are met (see milestones).

If the trial is prematurely discontinued, active participants will be informed and no further participant data will be collected. The Competent Authority (CA) and all relevant HRECs will be informed within 15 days of the early termination of the trial.

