## Interventions

The intervention under test is rifampicin (rifampicin) tablets 300 mg twice daily and the comparator treatment is ursodeoxycholic acid (UDCA) tablets up to 2000 mg daily, prescribed as per the usual local protocols.

Women meeting the inclusion criteria and consenting to participation will be randomly allocated to treatment with rifampicin or UDCA at study entry. The duration of treatment will range from 1 day to a maximum of 28 weeks, for a participant randomised at 14 weeks who does not deliver until 42 weeks.

Within the trial, both UDCA and rifampicin are usually dispensed by the local hospital pharmacy.

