Miscarriage (fetal death before 20^+ 0^ weeks gestation)Stillbirth (death before delivery ≥20^+ 0^ weeks gestation or > 400 g if gestation unknown)Neonatal death in hospital up to 7 days after birth (excluding death due to congenital anomalies)Neonatal unit admissions until infant discharge home from hospitalNumber of nights in each category of care (intensive, high dependency, special, transitional and normal) and total number of nights in hospitalBirth weight (g), and customised/population birth weight centile (GROW) [33]Apgar scores at 1 and 5 min after birthUmbilical arterial and venous pH (and base excess) at birthCord blood BANeed for supplementary oxygen prior to discharge, and number of days when such oxygen is requiredNeed for ventilation support (continuous positive airway pressure - CPAP/high flow/endotracheal ventilation)Pneumothorax (confirmed on chest X-ray)Need for phototherapyAbnormal cerebral ultrasound scanConfirmed sepsis (positive blood or cerebrospinal fluid cultures)Necrotising enterocolitis (Bell’s stage 2 and 3)Seizures (confirmed by EEG or requiring anticonvulsant therapy)Encephalopathy grade (worst at any time: mild, moderate, severe)Hypoglycaemia (blood glucose < 2.6 mmol/l on two or more occasions)Severe hypoglycaemia (blood glucose < 1.8 mmol/l on two or more occasions)Other indications and main diagnoses resulting in NNU admission.Mode of feeding at discharge from hospital

The primary outcome, maternal pruritus score, will be evaluated at 1 week after trial entry and then on a monthly basis up to 28^+ 0^ weeks gestation and then weekly to delivery.

The timepoints of evaluation of the secondary maternal outcomes are at 1 week post-randomisation visit, at monthly clinic visits at 20, 24 and 28 weeks gestation (if randomised prior to that), at weekly clinic visits after 28 weeks gestation and during admission for birth, and of the secondary neonatal outcomes at delivery and 1 week and 6 weeks after birth.

The following information post enrolment will be captured for health resource use:
Maternal: total number of nights (antenatal, intrapartum and postnatal) together with level of care including adult ICU.Infant: total number of nights for the baby in neonatal unit, together with level of care (e.g. neonatal ICU).

The costs of UDCA and rifampicin, together with the costs of any additional treatment, will be calculated in both the UDCA and rifampicin groups.

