**Table 1 Tab1:**
[figure not shown]
Trial Timeline

*GA* gestational age, *ALT* alanine transaminase, *LFTs* liver chemistry analysis, *INR/APTT* International Normalised Ratio/Activated Partial Thromboplastin Time

Notes to Table 1

^1^All screening assessments are part of normal clinical practice

^2^Bile acid samples need to be drawn shortly before a scheduled dose of UDCA, though fasting is not required. Women previously prescribed UDCA for treatment of mild ICP, and agreeing to randomisation, will have basal assessments performed 4–7 days after ceasing such therapy prior to randomisation into the trial

^3^Study treatment started after randomisation. Dose to be adjusted by PI if indicated by symptoms and/or blood tests taken during normal clinical practice

^4^Adverse events will be recorded from study entry until post-delivery discharge of woman and baby. All SAEs are to be reported to the Coordinating Centre within 24 h of Investigator knowledge

Women eligible for the trial, whether or not they participate, will be asked about their willingness to take part in a subsequent trial of planned delivery of such affected women at 36^+ 0^ weeks gestation compared with expectant management in terms of neonatal outcomes.

Women taking part in the study will be asked about any other drugs that have been prescribed or initiated after randomisation. If such medications include agents known to have a significant interaction with rifampicin, then a woman taking rifampicin will be asked to withdraw from the study, although any data obtained until withdrawal will be included, and any pregnancy outcome data will be recorded (with her consent).

Participating women will also be asked at recruitment about any antibiotics they may have taken in the 3 months prior to recruitment, as well as any progesterone supplements they may have taken.

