### Expected events

The following are considered as expected occurrences in this population of pregnant women or a result of the routine care/treatment of a participant. As such, they will be recorded on the eCRF but not reported as AEs or SAEs:
Worsening pruritusHospitalisation for worsening ICPGestational diabetes/diabetes stabilisationPre-eclampsiaAdmission in active labourAdmission for cervical ripening or induction of labourAdmission for caesarean sectionShort term (< 24 h) admission for assessment for suspected fetal compromise, including reduced fetal movements, or accelerated fetal growth and/or polyhydramniosShort term (< 24 h) admission for monitoring for hypertension, suspected preterm labour, or pre-labour rupture of the membranes

Such admissions are not AEs, but the underlying reason may be.

However, admission for other fetal or maternal issues, including IUGR, reduced movements, severe hypertension, seizures (eclampsia), antepartum haemorrhage, pre-term labour, pre-term premature rupture of the membranes (PPROM), psychiatric disorder, social issues, unstable lie/abnormal lie, amnioreduction, and other issues are to be reported as AEs, and may well be considered SAEs, especially if the admission is for > 24 h.

The following perinatal outcomes are pre-specified outcomes and will not be reported as AEs/SAEs:
NNU admissionPreterm delivery (< 37 completed weeks gestation)Meconium staining of the amniotic fluid or placentaNeed for phototherapyNeed for respiratory support – headbox oxygen

The following perinatal complications are to be reported as AEs and may be considered as SAEs:
Neonatal seizuresEncephalopathy treated with hypothermiaNeed for respiratory support – ventilation via an endotracheal tube or nasal CPAPSepsis requiring > 5 days antibiotics with symptoms or confirmed blood or cerebro-spinal fluid (CSF) culture

The period for safety reporting is from first dose of study treatment until 6 weeks post-delivery.

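### If the trial stops early, the stated rule ends all data collection, which conflicts with the protocol's own safety follow-up and leaves ongoing pregnancies with less follow-up than an individual withdrawal

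*Protocol article*

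**What the plan says.** The Treatment stopping rules section describes a data safety monitoring committee (DSMC) review after 50 women and gives the trial management committee the final decision on stopping for safety. It then sets a general rule for premature discontinuation, not tied to any reason: "active participants will be informed and no further participant data will be collected".

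Other sections set follow-up duties that extend beyond a possible stopping date:

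- Expected events: "The period for safety reporting is from first dose of study treatment until 6 weeks post-delivery".
- Procedures for recording AEs: "All AEs and SAEs will be followed-up to resolution with a start date and an end date recorded".
- Notes to Table 1, with a different end point: "Adverse events will be recorded from study entry until post-delivery discharge of woman and baby".
- Secondary outcomes, on timing of assessment: "of the secondary neonatal outcomes at delivery and 1 week and 6 weeks after birth". The Subsequent visits section adds a maternal visit at 6 weeks postpartum.
- Withdrawal of participants, for a woman who leaves on her own: "Permission will also be sought to ascertain and record subsequent perinatal outcome data"; and, on the reason for leaving, "if it was due to an Adverse Event, the investigator will follow up to resolution/stability".
- Notes to Table 1 also provide that a woman on rifampicin who is asked to withdraw because of an interacting drug still has her pregnancy outcome recorded, with her consent.

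**The concern.** Stillbirth, neonatal death, preterm birth and neonatal morbidity are unknown until birth or later. A woman randomised shortly before a stop may be weeks or months from that point. If the stop is for suspected harm, the pregnancies then in progress are among the most informative about whether the harm is real, and the rule tells sites to stop recording them. Sites would hold conflicting instructions: close adverse events with an end date, report safety to 6 weeks after delivery, and collect nothing more.

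The order of follow-up is also odd. The article accepts consented follow-up after a woman leaves the trial, but drops it when the whole trial ends. The analysis is meant to include all randomised women and babies by allocation (Data analysis section), which cannot be done for perinatal outcomes that were never collected.

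**Working it through.** **1. The texts side by side, for a woman randomised before the stop**

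| Her status at the stop | Follow-up required elsewhere | Under the stopping rule |
|---|---|---|
| Still pregnant | Safety to 6 weeks after delivery (Expected events), or to discharge after delivery (notes to Table 1); neonatal outcomes at birth, 1 week and 6 weeks | None |
| Delivered and discharged, less than 6 weeks ago | Safety to 6 weeks; 6-week maternal visit and neonatal assessment | None |
| Adverse event still open | Follow-up to resolution with an end date | None |
| Withdrew individually (comparison) | Perinatal outcomes with permission; an adverse event that caused withdrawal followed to resolution or stability | Not addressed |

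The two adverse event windows differ from each other (6 weeks after delivery against discharge). For a woman still pregnant the rule conflicts with both, so the conflict does not depend on which window is intended.

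**2. How long the gap can be for one woman**

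The Interventions section states: "The duration of treatment will range from 1 day to a maximum of 28 weeks, for a participant randomised at 14 weeks", with birth at 42 weeks.

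- Reproducing that figure: 42 − 14 = 28 weeks. It agrees.
- Adding the 6-week safety window: 28 + 6 = 34 weeks of uncollected follow-up at most, for entry at 14+0 just before a stop.
- For entry at 33+6 (33.86 weeks) just before a stop, with birth assumed at 37 to 42 weeks: 37 − 33.86 + 6 = 9.1 weeks, up to 42 − 33.86 + 6 = 14.1 weeks.

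**3. How many women**

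The article gives neither a recruitment rate nor a mean time from entry to birth, so both are assumptions. Under steady recruitment, the number still pregnant is roughly the monthly rate times the months from entry to birth. Take 6 to 10 weeks, that is 6/4.33 = 1.4 to 10/4.33 = 2.3 months.

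| Assumed rate per month | Still pregnant, low | Still pregnant, high | As a share of 50 women |
|---|---|---|---|
| 1 to 2 | 1 × 1.4 = 1.4 | 2 × 2.3 = 4.6 | 3% to 9% |
| 3 to 5 | 3 × 1.4 = 4.2 | 5 × 2.3 = 11.5 | 8% to 23% |

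Women delivered within the last 6 weeks are additional.

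**4. What truncation does to comparisons**

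At a calendar cut-off, a woman randomised five weeks earlier contributes a birth only if she delivered within five weeks. Short intervals to birth are therefore over-represented among recent entrants, and gestation and preterm birth summaries within each arm shift. The contrast between arms is distorted if treatment affects time to birth, or if the decision to stop depends on the accruing outcomes. The first is possible, since length of gestation is a secondary hypothesis. The second is likely in a safety stop. The direction cannot be stated from the article.

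**The case against.** The best defence is that the adverse event sections govern a running trial and the stopping rule is a specific exception for one that has ended. On that reading the clash is narrower. It still covers adverse events open at the stop and women inside the safety window, and nothing in the article says those duties lapse. The general provision for protocol amendments and the reference to national safety reporting guidelines do not alter the sentence.

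Several stronger readings are tempting, and the article does not support them.

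- *That the rule applies only to safety stops.* Safety is the only ground named, but the sentence is general. The same section mentions recruitment milestones and the Discussion reports pandemic difficulties. A stop for another reason would trigger the same rule, but the argument about losing evidence on a harm signal would then be weaker.
- *That the data would be destroyed.* Many birth and neonatal items are ordinary clinical records and would still exist. The plan simply does not provide for collecting them for the trial.
- *That every perinatal comparison would be biased.* A common cut-off truncates both arms, and bias between arms needs one of the conditions in step 4.
- *That a large, known share of women is affected.* The share rests on assumed accrual. Low rates are plausible for a disorder that the Background puts at 0.1% per annum.
- *That the primary result is at risk.* Pruritus is first scored at 1 week and analysed with repeated measures, so most women would already have contributed. A trial that runs to completion is untouched.

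**Conclusion.** The point holds as a wrongly stated rule, not as missing detail. As written, the stopping clause cannot be followed together with safety reporting to 6 weeks after delivery, follow-up of adverse events to resolution, or even the shorter window in the notes to Table 1. It also treats women in a stopped trial less fully than women who withdraw. The gap for one woman can reach 34 weeks, from the article's own figures. The number still pregnant at a stop is roughly 1 to 5 at 1 to 2 recruits per month and 4 to 12 at 3 to 5 per month, assuming 6 to 10 weeks to birth; the conflict itself needs none of these assumptions. The consequence is conditional on an early stop, and is most serious if the stop is for safety. Power, randomisation and the analysis of a completed trial do not change.

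**What to change.** Replace the clause with wording to this effect: if the trial is discontinued early for any reason, recruitment ends and participants are informed; with consent, perinatal outcomes and all AEs and SAEs continue to be collected for every randomised woman and baby to the end of the safety window, with open events followed to resolution, and are analysed as randomised.

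In the same amendment, reconcile the Treatment stopping rules, Expected events, Procedures for recording AEs and Withdrawal of participants sections and the notes to Table 1, so that one end point for adverse event recording applies throughout. Itch scoring after a stop is not needed to repair this defect. The change concerns data collection only and says nothing about treatment after a stop.

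The cost is one sentence, a line in the consent material if it does not already cover this, and a small amount of follow-up, largely through routine records. It is best settled before any stop, because permission is harder to obtain once sites have closed.
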